#### Secondary outcomes

2.9.2

Like primary outcomes, secondary and additional outcome data, with the exception of qualitative data (see below), are acquired at both pre-intervention and post-intervention assessment visits (see Figure 1).

##### Functional connectivity and structural integrity of relevant neural networks

2.9.2.1

Imaging is performed on a 3 T MRI system (Siemens MAGNETOM Skyra) with a 64-channel radiofrequency (RF) coil. Anatomical scans are acquired using a 3D T1-weighted (T1w) magnetization prepared rapid gradient-echo (MP-RAGE) pulse sequence with the Generalized Autocalibrating Partially Parallel Acquisition (GRAPPA) enabled to reduce acquisition time [repetition time (TR) = 2,400 ms; TI = 1,000 ms; time to echo (TE) = 2.32 ms; flip angle = 8°; field of view (FOV) = 230 mm × 230 mm; matrix size = 255 × 255; in-plane resolution = 0.9 mm; slice thickness = 0.9 mm; slices = 192; slice spacing = 0; acceleration factor = 2; acquisition orientation = sagittal]. A fluid attenuated inversion recovery (FLAIR) sequence is used to screen for clinically significant white matter (WM) abnormalities [0.9 mm^2^, 192 slices, FOV read = 230 mm, TR = 5,000 ms, TE = 387 ms, inversion time (TI) = 1800 ms].

Next, to address specific study aims, the following three imaging methods are used to assess functional connectivity between select grey matter regions, and integrity of the relevant white matter tracts.

1. Resting state functional MRI (rs-fMRI): Functional scans sensitive to the T2-weighted blood-oxygen-level dependent (BOLD) signal are collected using a 2D gradient echo pulse sequence with interleaved acquisition [TR = 800 ms; TE = 38 ms; flip angle = 52°; FOV = 210 mm; matrix size = 84 × 84; in-plane resolution = 2.5 mm; slice thickness = 2.5 mm; slices = 54; slice spacing = 0; acquisition orientation = axial; interleaved, Siemens Simultaneous Multi-Slice (SMS) = 6 and Siemens integrated-Parallel Acquisition-Techniques (iPAT) = 2].

Detailed data preprocessing methods are provided in the supplement. Briefly, T1w and BOLD images are preprocessed using fMRIPrep 20.2.7 (Esteban et al., 2018a,b). T1w images are corrected for intensity non-uniformity (INU), skull-stripped, and then normalized to standard space (MNI152NLin2009cAsym). For each of the BOLD runs, a B0-nonuniformity map (or fieldmap) is estimated based on a phase-difference map calculated with a dual-echo GRE (gradient-recall echo) sequence used to correct for distortion. BOLD images are then co-registered to the T1w reference. Co-registration is configured with six degrees of freedom. Automatic removal of motion artifacts is completed using independent component analysis.

2. 3D-gradient and spin-echo (GRASE): Multi-echo T2 relaxation images are acquired in the transverse plane with a sequence (Prasloski et al., 2012). The duration of the GRASE sequence is 10.03 min (1.9 × 1.9 × 4 mm, 32 slices, distance factor 50%, TR = 1,000 ms, number of echoes = 32, first echo = 10 ms, echo spacing = 10 ms, flip angle = 90 degrees, FoV read = 240 mm).

3D GRASE images are fitted using an in-house script in Matlab (Prasloski et al., 2012). In brief, we use fitting of multiple exponential functions with stimulated echo correction using an extended phase graph to generate a T_2_ distribution from the multi-echo data. To improve the reliability of the fitting, we use Tikhonov regularization, which enforces minimum energy and generates a smooth T_2_ distribution. Finally, a myelin water fraction (MWF), which is the ratio of myelin water signal to total water signal, is calculated at each voxel. We used the integration ranges 10 ms – 40 ms for myelin water pool and 40 ms – 2000 ms for the axonal/extracellular water pool. Then, the first echo images from the 3D GRASE acquisition are linearly registered to the unwarped b = 0 diffusion-weight images (DWI) maps (6 degrees of freedom, 180 degrees search function, interpolation, sinc 15, see below), and this transformation is then applied to the individual MWF maps so that they are aligned with the b = 0 images, and, therefore, fractional anisotropy (FA) images.

3. Diffusion-weighted images (DWI) are acquired in the anterior-to-posterior phase encoding direction using a multi-shell (b = 0, 1,000, 2000) high-angular-resolution (138 directions) multiband echo planar sequence in transversal plane (1.8 mm3 voxels size, 76 slices, TR = 3,120, TE = 104.8, multiband acceleration factor = 4, flip angle = 79 degrees, refocus flip angle = 160 degrees). Then, the scan is repeated in the posterior-to-anterior phase encoding direction for one b = 0 image. This acquisition is designed to allow for fitting the Neurite orientation dispersion and density imaging (NODDI) model to the data, which combines a multi-shell high-angular-resolution diffusion imaging with three-compartment tissue modelling (intra-, extra-cellular and CSF; Le Bihan, 1995; Zhang and Meerschaert, 2011; Zhang et al., 2012). NODDI provides voxel-wise estimation of intra-cellular volume fraction (ICVF) reflecting axonal density, orientation dispersion index (ODI), and isotropic volume fraction (FISO; Zhang et al., 2012). Separate measurement of ICVF and FISO is critical for differentiating demyelination with and without axonal loss.

From the pairs of the DWIs acquired with reversed phase-encoding blips, susceptibility-induced off-resonance field is estimated (Andersson et al., 2003), as implemented in functional magnetic resonance imaging of the Brain Software Library (FSL) as top-up (Smith et al., 2004) generating a single corrected (or unwarped b = 0 image). Then, the top-up distortion correction is applied using eddy in FSL (Andersson and Sotiropoulos, 2016), which also corrects for distortions related to eddy current and motion. The diffusion tensor model can be fitted to the data using the FSL Diffusion Toolbox v.5.0 (FDT), yielding the FA maps. In addition, the NODDI model is fit to the data using NODDI toolbox in Matlab. All steps of image processing and registration are visually inspected. Finally, we use the tract-based spatial statistics (TBSS) (Smith et al., 2007) workflow in FSL v6.0.5.2. In brief, this includes: (a) nonlinear alignment of each participant’s FA volume to the 1 × 1 × 1 mm 3 standard Montreal Neurological Institute (MNI) space via the FMRIB58_FA template using the FMRIB’s Nonlinear Registration Tool (FNIRT, Rueckert et al., 1999),^2^ (b) calculation of the mean of all aligned FA images, (c) and the option to create a WM “skeleton” (a representation of WM tracts common to all subjects) by perpendicular non-maximum-suppression of the mean FA image and setting the FA threshold to 0.2, (d) perpendicular projection of the highest FA value (local center-of-tract) onto the skeleton, separately for each subject. Finally, we apply tbss_non_FA procedure to MWF and NODDI maps aligned with the unwarped b = 0 images, yielding MWF, FISO, and ICVF values projected on the skeleton.

##### Region of interest analysis

2.9.2.2

To evaluate potential differences in specific WM tracts, we first estimate myelin content in the entire WM by averaging the MWF values from the entire skeleton for each participant (whole WM). Next, we extract mean MWF values from regions representing the major association, projection, and commissural fibers, as described previously (Burzynska et al., 2013), using the diffusion tensor imaging (DTI) white-matter atlas (Mori et al., 2005), with the aim to include the core regions specific to each tract. The corpus callosum is segmented so that genu represents prefrontal commissural fibers, body containing premotor, supplementary motor, motor and sensory fibers, and splenium containing parietal, temporal and occipital connections (Hofer and Frahm, 2006). The prefrontal WM region is defined as y > 12 in MNI coordinate space and whole WM included the whole TBSS skeleton. The cingulum includes both the ventral and dorsal segments, and the corticospinal tract is represented by the core regions of the superior corona radiata, posterior limb of the internal capsule, and the cerebral peduncles. The uncinate is probed in the lateral ventral prefrontal region as well as in the section along the fronto-occipital fasciculus. Mean MWF are extracted from each region using fslmeans in FSL.

##### Task-dependent neural activation

2.9.2.3

These data are acquired via a single method using a portable fNIRS device, the NIRSport2 (nirx.net), during the second balance assessment method (see above for description).

FNIRS measures neural activation, via proxy measures of oxygenated hemoglobin (HbO) and deoxygenated hemoglobin (HbR), derived from superficial cortical regions. For this study, we are evaluating balance-task dependent activation in two ROI - bilateral inferior parietal and motor cortices, as these regions support postural control and balance (Surgent et al., 2019). To measure from these regions, we used the fNIRS Optodes’ Location Decider (fOLD) toolbox (Zimeo Morais et al., 2018) in Matlab to place thirty total optodes-15 light sources and 15 light detectors - over the ROIs in an fNIRS acquisition cap. Additionally, eight short separator detectors are included on the underside of the fNIRS cap to measure scalp perfusion, a nuisance variable, which is removed during data processing (Brigadoi and Cooper, 2015; Sato et al., 2016). FNIRS data are acquired via Aurora Version 2021.9 software (nirx.net).

Following acquisition, fNIRS data files are processed using Satori version 1.8.^3^ Preprocessing steps of conversion and spatial registration are performed automatically by Satori. Specifically, in the conversion step, the raw light intensity data are converted to optical density values and then converted to total hemoglobin (HbT), HbO and HbR values using the Modified Beer–Lambert Law (Baker et al., 2014). Then, all data are spatially registered to the fNIRS head probe and displayed for visual inspection. Following these automated steps, the data are segmented into ‘events,’ which represent the four balance tasks and their durations. Next, temporal pre-processing steps of motion artifact detection and correction are completed with a spike removal procedure that uses the Satori default parameters (10 iterations, 5 s lag, 3.5 threshold, 0.5 influence). A monotonic interpolation is applied in instances of spike detection. Next, to restore high frequency bands, the Temporal Derivative Distribution Repair (TDDR) (Fishburn et al., 2019) is used. To remove physiological noise, three steps are completed. First, a generalized linear model (GLM), which uses the highest correlation method to automatically select channels with artifacts, is completed for short separation regression (SSR). Next, low-frequency drifts as well as part of the non-hemodynamic related signal components such as heart rate are removed in a temporal filtering step using a Butterworth high-pass filter and then a Gaussian low-pass smoothing filter with cut-off frequencies of 0.01 Hz and 0.4 Hz, respectively. Finally, a normalization step using Z-transform is completed to make data comparable between subjects. Given the relativeness newness of Satori software, the default setting that automatically rejects channels with a scalp coupling index (SCI) below 0.75 (Pollonini et al., 2014) is not used. Instead, all data are processed without automated channel rejection (these are the data used group-level analyses), and then the raw data are processed again with the automated channel rejection step. This step generates a channel rejection map that indicates which channels would be rejected and their SCI value. This information is used to check data for potential outliers after group-level analysis. After all pre-processing was completed, group-level data can be generated using a multi-subject GLM approach within Satori.

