#### fNIRS data

2.14.3

HbO and HbR beta values will be used in a mixed effects model to assess prospective within and between-group differences, along with interaction effects, in neural activation over ROIs.

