#### Secondary outcomes

4.1.2

There is limited research on yoga on for brain injury, especially regarding its impact on the integrity neural networks and task-dependent brain activity. However, there is evidence from healthy populations and pilot data from our lab to inform our hypotheses. Specifically, in healthy individuals yoga can enhance structure and function of brain regions and neural networks, such as the default mode network (Gothe et al., 2019). Additionally, in adults with chronic acquired brain injury, pilot data from our lab suggests improved neural efficiency during balance tasks (Stephens et al., 2023). Based on these findings, we hypothesize that participants in the group yoga will have greater improvements in neural network integrity. We also expect to see decreased task-dependent brain activity in the yoga group, which would suggest improved neural efficiency after yoga.

Finally, we expect that yoga will have a significantly greater impact on cognitive function and quality of life. A recent meta-analysis showed yoga interventions improve cognition and quality of life in individuals with TBI (Acabchuk et al., 2021). Although this study did not include individuals with acquired brain injuries, we anticipate similar findings in our population.

In summary, we hypothesize that our protocol will elicit improvements in both groups, particularly on balance performance. However, given prior literature – mostly conducted with healthy populations – we predict that the unique features of yoga will have a significantly greater impact on ANS function, integrity of neural networks, task-dependent brain activity, cognition and quality of life.

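### The fNIRS channel-quality map is consulted only after the group-level analysis, with poorly coupled channels left in: a risk of result-influenced exclusion and of diluted ROI betas

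*Protocol article*

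**What the plan says.** Section 2.9.2.3 (Task-dependent neural activation) describes two processing runs.

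- The software has an automatic quality filter, "the default setting that automatically rejects channels with a scalp coupling index (SCI) below 0.75", and the trial does not use it. The reason offered is "Given the relativeness newness of Satori software".
- For the main run, "all data are processed without automated channel rejection (these are the data used group-level analyses".
- The raw data are then processed again with the filter on. "This step generates a channel rejection map that indicates which channels would be rejected and their SCI value".
- On the use of that map: "This information is used to check data for potential outliers after group-level analysis".

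The same section lists visual display of the data, spike removal, TDDR, short-separation regression and filtering, and then says that "a normalization step using Z-transform is completed to make data comparable between subjects". Group-level data are generated by a multi-subject GLM once pre-processing is finished.

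Section 2.14.3 gives the inferential step: "HbO and HbR beta values will be used in a mixed effects model", with within-group, between-group and interaction effects. Section 4.1.2 states the hypothesis: "We also expect to see decreased task-dependent brain activity in the yoga group". Section 2.15 handles missing data by removal without imputation.

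**The concern.** Optode coupling is a property of the recording. It can be judged without arm, visit or outcome, and the map that shows it needs only the raw files. The article nevertheless places the quality check after the group-level analysis. A doubtful channel or participant is then examined when at least some group result is known, and no criterion or consequence is stated. The newness of the software is a reason to check the automatic filter by eye. It is not a reason to wait for the result before doing so.

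Two things are at stake. First, if the check leads to exclusions, they may be influenced by what the result looked like, and the nominal error rate no longer holds. Second, channels with little usable signal remain in the ROI summaries. The listed cleaning steps address motion and physiological noise, and none is described as excluding a channel for poor coupling. After the Z-transform, a channel that is mostly noise has the same variance as a good one, so it can contribute at full weight while adding little task response.

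**Working it through.** The article states no error rate or power for the fNIRS outcome, so there is no figure to reproduce. The order of steps is read from the text; the sizes below are illustrations on assumed inputs.

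**Order of steps**

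1. Main run, no channel rejection (2.9.2.3).
2. Second run, giving the SCI map (2.9.2.3).
3. Group-level analysis on the unrejected data (2.9.2.3).
4. SCI map used to look for outliers (2.9.2.3).

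Step 2 needs nothing from step 3, so step 4 could come before step 3 with no new data. Section 2.7 unmasks the PI once post-intervention assessments are completed and scored, and no masking is stated for step 4.

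**Illustration A: error rate if either version could be reported**

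Inputs: two-sided alpha 0.05 (0.05 is the level in Section 2.5; two-sided is assumed); correlation r between the all-channel and screened test statistics, assumed 0.7 to 0.9.

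Formula: error = 1 − P(|Z1| < 1.96 and |Z2| < 1.96), with Z1 and Z2 standard bivariate normal with correlation r.

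| r (assumed) | P(neither significant) | Error |
|---|---|---|
| 0.9 | 0.930 | 7.0% |
| 0.8 | 0.922 | 7.8% |
| 0.7 | 0.917 | 8.3% |

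A separate null simulation used 18 per arm (half of the 36 in Section 2.5), 15 channels, 10% to 30% bad channels and 10,000 runs per setting. Everything except the 36 is assumed.

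| Rule | Simulated error |
|---|---|
| One analysis fixed in advance | 4.7% to 5.4% |
| Smaller p-value of all-channel and screened | 6.2% to 7.5% |
| As above, plus dropping participants with more than one third bad channels | 7.0% to 9.4% |

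**Illustration B: dilution**

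Inputs: share f of ROI channels with no task signal (not in the article; assumed 10% to 40%); ROI beta taken as an equal-weight mean of channels (assumed); 18 per arm; true standardised difference d = 0.8 with SD held at 1 (assumed).

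Formulas: diluted effect = (1 − f) × d. Power ≈ Φ[(1 − f) × d × √(18/2) − 1.96].

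At f = 0: Φ(0.8 × 3 − 1.96) = Φ(0.44) = 67%. At f = 0.2: Φ(0.64 × 3 − 1.96) = Φ(−0.04) = 48%.

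| f (assumed) | Effect retained | Power at d = 0.8 |
|---|---|---|
| 0 | 100% | 67% |
| 0.1 | 90% | 58% |
| 0.2 | 80% | 48% |
| 0.3 | 70% | 39% |
| 0.4 | 60% | 30% |

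These use the normal approximation; the noncentral t gives values one to three points lower. The direction follows from the formula. The size depends wholly on f and on how channels are combined.

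**The case against.** Four objections deserve weight.

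- **The analysis set is fixed.** The article names the unrejected data as the data for group-level analysis and says the map is used to check. It does not say that channels will be removed, that the model will be rerun, or that the screened version may be reported. A reader might infer that the sponsor intends to choose between two results; the text does not support that. This stands, and it makes the error rates in illustration A conditional.
- **Group-level may not mean yoga versus exercise.** In Section 2.9.2.3 the term is tied to the multi-subject GLM in the fNIRS software, while the arm comparison is the mixed model of Section 2.14.3. The check could fall between the two. The ambiguity is real, so it cannot be said that the arm contrast is certainly known at that point. But the order as written does not exclude it, and the check still follows a group result.
- **Keeping all channels is defensible.** As a choice fixed in advance it is, and screening loses data in a small trial. This stands. The weakness is the timing of the check, not the all-channel analysis as such.
- **The rest is detail for a fuller document.** An outlier criterion could sit in an analysis plan that is not shown, and its absence alone would be no finding. But the article itself states that the check comes after the group-level analysis.

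A further inference is tempting. Lower activation is the hypothesised benefit, so poorer coupling at the yoga arm's post-intervention visit would mimic it. Nothing in the article suggests coupling would differ by arm. Dilution that is equal across arms and visits makes a difference harder to detect and does not create a yoga advantage.

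**Conclusion.** The point holds as a risk arising from a stated sequence. Channels that would fail the SCI threshold stay in the group-level fNIRS data, and the quality map is used only afterwards, with no stated masking or consequence. This leaves room for result-influenced exclusion and lets signal-poor channels dilute the ROI betas.

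If either version could be reported, which the article does not say, the two-sided 5% error would be about 7% to 8%, for an assumed correlation of 0.9 to 0.7 between versions. With equal-weight averaging, dilution shrinks the effect in proportion to the share of signal-free channels. That share is unknown, so no single figure can be given for this trial.

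The outcome is secondary and the trial is a pilot, so this is a change that should be made. It does not touch the primary outcomes.

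**What to change.** Move the SCI review ahead of the group-level analysis:

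1. Review the SCI map of each recording masked to arm, before any group-level GLM or mixed model is run.
2. Lock the list of excluded channels and participants at that point, with the rule that produced it.
3. Make no exclusions from the main analysis once a group result has been seen.
4. Preferably use the SCI-screened data as the main analysis and report the all-channel data as a sensitivity analysis. If the sponsor keeps all channels as main, lock that choice and report the screened version only as a prespecified sensitivity analysis.

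Both processing runs are already made, so no new data and almost no extra work are needed. The cost is that some channels are lost if screening is applied. With removal and no imputation under Section 2.15, a participant whose ROI has no usable channel would drop out of that comparison.

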##### Cognition

2.9.2.4

Acquired via selected assessments from the NIH Toolbox Cognition Battery (Tulsky et al., 2014; Zelazo et al., 2014). The selected assessments include the List Sorting Working Memory Test which assesses working memory via tasks that require sequencing of visual and auditory stimuli, the Flanker Inhibitory Test which assesses inhibitory control and attention using a series of picture pairs, and the Dimensional Change Card Sort Test which assesses cognitive flexibility using target pictures. For each assessment, the NIH toolbox app converts raw scores to standardized scores for interpretation of performance. Specifically, for each assessment, raw scores are automatically converted into T-scores, along with an age-scored standard score (higher indicates better performance) and an age-adjusted national percentile (0–100%), which shows how the participant compares to age- and sex-matched peers (higher also indicates better performance).

##### Self-reported quality of life

2.9.2.5

Acquired via the Traumatic Brain Injury Quality of Life (TBI-QOL) Short Form Measure on NIH Toolbox app (Tulsky et al., 2016). The NIH toolbox app converts raw scores to standardized scores for interpretation of performance. Specifically, raw scores are automatically converted into a metric, called T-scores. For short-form measures, the T-score Mean is 50, with a Standard Deviation of 10. T-scores above 50 indicate that individuals are having more problems in quality of life than age-and sex-matched individuals in the general population, whereas scores below 50 indicate that they are having fewer problems (Tulsky et al., 2016).

